### Data management

All patient data and electronic files will be stored in the secure environment of the Chronic Viral Illness Service of the McGill University Health Centre, (Montreal, Quebec, Canada) and in the CTN database (Vancouver, British Columbia, Canada). All data will be anonymized for publication. Only researchers affiliated with the study will have access to participant data. Study progress and safety will be evaluated in an ongoing fashion by a CTN Data and Safety Monitoring Committee (DSMC).

### Storage of biological specimens

Biological samples will be stored at the Chronic Viral Illness Service of the McGill University Health Centre for analysis in the current trial and for future use in ancillary studies.

### Adverse events

The safety and tolerability of Niaspan FCT will be evaluated by vital signs and AE monitoring, both spontaneously reported by the participant and actively sought at each clinic visit. In addition, biological tolerability will be evaluated by hematology, biochemistry and any other clinical, laboratory or diagnostic tests conducted on the participants during the course of the study. The trial medical monitor and the trial investigator will receive and review the lab results for all participants for all assessed safety variables. The DSMC will also review safety information. The toxicity of Niaspan FCT will be assessed using the World Health Organization toxicity scale. Any AEs and laboratory abnormalities that occur during the study will be evaluated by the trial investigators and grade 3 and 4 AEs will be recorded on case report forms (CRFs). Grades 1 and 2 AEs specific to the effects of flushing will also be recorded on the CRFs. The ‘Bays-Ballantyne niacin-induced flushing and persistence of use questionnaire’ will be used during ER niacin administration to follow the participants’ perception of the side-effect of flushing [54]. If required, blood specimens will be collected for hematology and biochemistry tests. Participants having AEs will be monitored with relevant clinical assessments and laboratory tests, as determined by the trial investigator. The trial investigator will report ongoing AEs at completion of the clinical study to the primary care physician, who will determine the need for, and provide, standard medical care. The trial investigator will ensure that the event is satisfactorily resolved or that no further follow-up is required. Any participants who discontinue participation for an unresolved clinically significant AE will be followed until satisfactory clinical resolution is achieved and the AE recorded on the CRF, regardless of severity grade. AEs that may be related to ER niacin administration will be managed by dose reduction of the study drug and/or by taking 325 mg acetylsalicylic acid (ASA) 30 minutes prior to ER niacin administration and/or by dosing at bedtime [55]. In the case of life-threatening AEs, ER niacin will be discontinued permanently.

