### Study outcome measures

The primary objective of this study will be to assess the impact of ER niacin supplementation in combination with ART compared to ART alone on T-cell immune activation as defined by changes in the percentage of CD8+ CD38+ HLA-DR+ T-cells.

The secondary objectives of this study will be to: 1) assess the change in total CD4+ T-cell count after ER niacin administration; 2) explore the effect of ER niacin on Th17 and Treg cell frequencies in blood; 3) explore the effect of ER niacin on cytokines and inflammatory markers such as interferon-alpha (IFN-α), IL-1, IL-6 and IL-17, interferon gamma-induced protein 10 (IP-10), D-dimers, highly-sensitive C-reactive protein (hsCRP) and LPS; 4) assess the influence of ER niacin on Trp plasma levels; 5) assess changes in cholesterol and triglyceride levels; 6) evaluate the impact of ER niacin on QoL, fatigue, depression and neurocognitive scores; and 7) explore ER niacin tolerance.

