Another objective of this study is to examine Niaspan FCT tolerance. Flushing at the initiation of niacin therapy is the most commonly reported side effect and is defined as redness, warmth, itching and/or a tingling sensation on the face, neck, chest and back [55]. This is a natural reaction signalling that niacin is in the bloodstream. Flushing is believed to be caused by an increase in blood flow and by the expansion of blood vessels close to the surface of the skin. Most participants on Niaspan FCT will experience this sensation, usually at the start of therapy or when the dosing is increased (occurring in up to 88% of participants in previous studies). These effects are usually transient and rarely require discontinuation of therapy (fewer than 6% discontinued due to flushing) [44]. Niaspan FCT, the drug to be administered in this pilot study, is an ER form of niacin that is dosed once each night when cholesterol synthesis and fatty acid mobilization are at their peak [38]. This form of niacin has intermediate-release characteristics and is thus designed to minimize both liver enzyme elevation and flushing. It is expected that for most participants, the flushing in response to ER niacin will occur over the first eight weeks of therapy and should become milder and less frequent as their bodies adjust to this drug.

For this pilot study, a convenience sample of 20 participants was chosen without formal power calculations. Should the results of this study suggest that niacin is tolerable, effective at reducing T-cell activation and/or has a positive effect on QoL, fatigue, depression and neurocognition, future studies will be performed. As a crossover study, two other comparisons will be made between the two arms: 1) the period of niacin plus ART in arm 1 will be compared to niacin plus ART in arm 2; 2) the period of ART alone in arm 1 will be compared to ART alone in arm 2. This will allow for the further evaluation of the potential continuity of the hypothesised effect of niacin following its discontinuation. The data obtained in this pilot study should be sufficient to assist in formal power calculations for such future studies.

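### The CRF rule leaves out grade 1-2 non-flushing adverse events in participants who stay in the trial, so the tolerance profile will be incomplete for mild and moderate events

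*Protocol article*

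**What the plan says.** All of this is in the protocol article.

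- **What is recorded.** Under Adverse events, the investigators evaluate all events and laboratory abnormalities, but only some are sent to the CRF. The general rule and its extension to low grades read: "grade 3 and 4 AEs will be recorded on case report forms (CRFs). Grades 1 and 2 AEs specific to the effects of flushing"; the latter are entered as well. A third category covers participants who leave the trial because of an unresolved, clinically significant event. They "will be followed until satisfactory clinical resolution is achieved and the AE recorded on the CRF, regardless of severity grade".
- **What is looked for.** The same section has events both reported spontaneously and actively sought at each clinic visit. Tables 3 and 4 mark adverse events, physical examination with vital signs, hematology and chemistry at every visit from week 0.
- **What may follow from an event.** "AEs that may be related to ER niacin administration will be managed by dose reduction of the study drug", and/or by ASA before the dose, and/or by bedtime dosing. No grade threshold is attached.
- **What the data are for.** Study outcome measures lists "7) explore ER niacin tolerance" as the last secondary objective. The Discussion names tolerance again as an objective, and its sentence on future studies opens: "Should the results of this study suggest that niacin is tolerable".

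**The concern.** The trial intends to describe how well ER niacin is tolerated in 20 people. In a group that small, severe events will be few, and much of what can be learned about tolerance is likely to lie in mild and moderate events. The recording rule captures those fully for flushing only. Other low-grade symptoms, such as gastrointestinal complaints (our example), are asked about at each visit but need not be written on the CRF if the participant continues.

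Two things are at stake. First, a short list of non-flushing events could reflect the recording rule as much as the drug, which makes it a weak basis for the tolerability part of a decision on further studies. Second, a low-grade event may lead to a dose reduction during a titration that Tables 1 and 2 take from 500 to 2,000 mg, without itself having to appear as an adverse event. When exposure falls short of the schedule, the adverse event data then need not show what preceded it.

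**Working it through.** The article gives no figure for event recording, so there is nothing to reproduce. The check is mainly a comparison of rules.

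**Step 1: sort the events by the stated rule.**

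| Event | Participant stays in the trial | Participant leaves because of it, unresolved and clinically significant |
|---|---|---|
| Grade 3-4, any type | CRF | CRF |
| Grade 1-2, flushing | CRF | CRF |
| Grade 1-2, not flushing | **no entry required** | CRF |

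One cell is empty: low-grade, non-flushing events in continuing participants.

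**Step 2: see whether another described instrument fills that cell.**
- Chemistry and hematology are done at every visit, so low-grade laboratory changes can be analysed from the values without an event line. Hepatic and metabolic effects are largely covered in this way, to the extent that the panel includes them.
- The Bays-Ballantyne questionnaire concerns flushing.
- The Simple Medication Adherence Questionnaire consists of seven binary adherence questions and does not collect symptoms.
- Concomitant medications are listed among the safety assessments under Clinical parameters, so ASA use has a place. The symptom that prompted it has none stated.

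What remains uncovered is mainly symptomatic non-flushing events of grade 1-2.

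**Step 3: compare with the dose rule.** A possibly related event of any grade may lead to dose reduction. An event in the empty cell can therefore change the study drug without requiring an adverse event entry.

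**Step 4: size, on assumed rates.** Inputs: n = 20 (Sample size and statistical analyses), all of whom receive ER niacin in one of the two periods; p = the share of participants with at least one event in the empty cell, assumed to be 10% to 30%.

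Expected number = n × p; chance of at least one = 1 − (1 − p)^20.

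| Assumed p | Expected number of 20 | Chance of at least one |
|---|---|---|
| 10% | 20 × 0.10 = 2 | 1 − 0.90^20 = 88% |
| 20% | 20 × 0.20 = 4 | 1 − 0.80^20 = 99% |
| 30% | 20 × 0.30 = 6 | 1 − 0.70^20 = 99.9% |

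Across this range, 2 to 6 participants would have an event that the CRF rule does not ask for.

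**The case against.** The best defence is that selective recording of low-grade events is a reasonable choice for a small pilot of a drug given as its product monograph recommends. The objective is only to "explore ER niacin tolerance". The Discussion describes tolerance almost wholly in terms of flushing, which is captured at all grades and by questionnaire. Vital signs and laboratory tests are done at every visit, events are still evaluated by the investigators, and a data and safety monitoring committee reviews safety. Much of this stands, and it rules out several stronger readings.

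- *A reader might infer that only severe events and flushing are ever recorded.* The discontinuation category contradicts that.
- *A reader might infer that the tolerance objective cannot be answered.* It can be answered in part, from flushing at all grades, severe events, events behind the discontinuations described, vital signs and laboratory values.
- *A reader might infer that dose reductions will have no recorded reason.* The article does not say so. A dosing form, which an article commonly leaves to the full protocol, may hold the reason. What the text supports is narrower: the event need not be entered as an adverse event.
- *A reader might point to the chance of seeing no grade 3-4 event in 20 people,* for example 0.95^20 = 36% at an assumed 5% risk. Such events are recorded under this rule and would be under any other, so the figure reflects the sample size and says nothing about the rule.
- *A reader might infer that the primary result could not be interpreted.* The primary comparison does not use dose or reasons for reduction, and exposure can be seen in part through the adherence questionnaire and the niacin levels measured during treatment.

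The defence does not remove the gap itself. The recording rule is stated in the article, so the gap does not come from condensing a longer document, and none of the instruments described covers symptomatic low-grade non-flushing events in continuing participants.

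**Conclusion.** The point holds in a limited form. As written, the CRF rule fits poorly with a tolerance objective that is also a ground for future studies: it omits grade 1-2 non-flushing events in participants who stay, including those that lead to a change in study drug. The tolerance profile will be incomplete for mild and moderate non-flushing events, mainly symptoms. On assumed rates of 10% to 30%, about 2 to 6 of 20 participants are affected. The size depends entirely on those assumed rates; the gap itself follows from the text. The Discussion sets no tolerance threshold, so the documents do not show that a wrong decision would follow. The change is still worth making because these events are already asked about at each visit and writing them down costs little.

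**What to change.** Change data capture only; the rules for managing events stay as they are.

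1. Record on the CRF every adverse event, of any grade, that is judged possibly related to ER niacin or that leads to dose reduction, ASA use, interruption or stopping. Give onset week, grade and action taken. Keep the existing categories.
2. Report tolerance as the proportion of participants with any such event, by grade, alongside the proportion who reach the scheduled dose and stay on it.
3. Trial status says the trial started in February 2012. For participants already enrolled, abstract these events from the visit notes where the notes allow, and mark them as retrospective in the report.

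The cost is a few more CRF lines per visit and limited abstraction, with no added visits or tests. The abstraction may be incomplete, so earlier participants could appear to have fewer low-grade events than later ones; the report should say so.

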### Ethics

Written informed consent will be obtained from all study participants. The study protocol and consent forms have been approved by the Research Ethics Board of the McGill University Health Center (reference number: 11-019GEN) and by Health Canada’s Therapeutic Products Directorate (reference number: 9427-M2303-44C). The study will be conducted in accordance with the applicable Health Canada regulations, International Conference on Harmonization guidelines on current Good Clinical Practice and the Declaration of Helsinki.

## Discussion

ART therapy has significantly decreased HIV-associated morbidity and mortality over the last 15 years. Despite the substantial benefits of ART, immune reconstitution may not be complete for approximately 30% of patients who achieve virologic control [1, 2]. These patients remain at an elevated risk for clinical progression to both AIDS and non-AIDS events [1, 3–5].

We have designed a proof-of-concept study to assess supplementation with Niaspan FCT (an ER form of niacin) in combination with ART, compared to ART alone, on T-cell immune activation as defined by changes in the percentage of CD3+ CD8+ HLA-DR+ T-cells. A reduction in immune activation may improve CD4 recovery in HIV-infected individuals with suboptimal immune responses despite sustained virologic suppression. Our study also includes a neurocognition substudy that examines the effect of niacin on QoL, fatigue and depression.

It has been previously reported that a 10-fold difference exists between uninfected healthy controls and treated aviremic HIV-infected participants in the level of activated CD3+ CD8+ HLA-DR+ T-cells [52, 56]. It is expected that a 50% reduction in activated CD3+ CD8+ HLA-DR+ T-cells will be observed following ER niacin treatment which should translate into a clinically significant increase in CD4+ T-cell count (>100 CD4+ T-cells/μL). This estimate is based on a mean increase of 100 CD4+ T-cells/μL for participants having a two-fold reduction or not in their CD8+ T-cell activation level after 48 weeks of ART [57]. Assessments of activated CD4+ CD38+ and CD8+ CD38+ cell subsets will allow, for the first time, a more precise definition of which cell subpopulation(s) may change with ER niacin. Measurements of circulating cytokines, inflammatory mediators and LPS will be used to determine whether ER niacin administration can reduce or suppress inflammatory mediators known to drive immune activation.

Another objective of this study is to examine Niaspan FCT tolerance. Flushing at the initiation of niacin therapy is the most commonly reported side effect and is defined as redness, warmth, itching and/or a tingling sensation on the face, neck, chest and back [55]. This is a natural reaction signalling that niacin is in the bloodstream. Flushing is believed to be caused by an increase in blood flow and by the expansion of blood vessels close to the surface of the skin. Most participants on Niaspan FCT will experience this sensation, usually at the start of therapy or when the dosing is increased (occurring in up to 88% of participants in previous studies). These effects are usually transient and rarely require discontinuation of therapy (fewer than 6% discontinued due to flushing) [44]. Niaspan FCT, the drug to be administered in this pilot study, is an ER form of niacin that is dosed once each night when cholesterol synthesis and fatty acid mobilization are at their peak [38]. This form of niacin has intermediate-release characteristics and is thus designed to minimize both liver enzyme elevation and flushing. It is expected that for most participants, the flushing in response to ER niacin will occur over the first eight weeks of therapy and should become milder and less frequent as their bodies adjust to this drug.

For this pilot study, a convenience sample of 20 participants was chosen without formal power calculations. Should the results of this study suggest that niacin is tolerable, effective at reducing T-cell activation and/or has a positive effect on QoL, fatigue, depression and neurocognition, future studies will be performed. As a crossover study, two other comparisons will be made between the two arms: 1) the period of niacin plus ART in arm 1 will be compared to niacin plus ART in arm 2; 2) the period of ART alone in arm 1 will be compared to ART alone in arm 2. This will allow for the further evaluation of the potential continuity of the hypothesised effect of niacin following its discontinuation. The data obtained in this pilot study should be sufficient to assist in formal power calculations for such future studies.

### Dissemination plan

The results of the trial, regardless of outcome, will be disseminated through the traditional routes of scientific peer-reviewed publications, through international and national specialist conferences, and through the CTN. BL and [name] will be responsible for initially drafting these manuscripts and professional writers will not be used for any of the publications. Authorship will be based on the criteria defined by the International Committee of Medical Journal Editors [58]. We aim to write the final results paper within six months of the un-blinding procedure. Subjects who have been involved in the trial will be given the option of having a summary of the results sent to them.

## Trial status

The trial was started in February 2012. We expect enrolment to be complete by November 2014.

## Abbreviations

3-OHK: 3-hydroxy-kynurenine
AE(s): Adverse event(s)
AIDS: Acquired immune deficiency syndrome
ALT: Alanine transaminase
ART: Antiretroviral therapy
ASA: Acetylsalicylic acid
AST: Aspartate transaminase
CANTAB: Cambridge Neuropsychological Test Automated Battery
CES-D: Center for Epidemiologic Studies Depression scale
CRFs: Case report forms
DC(s): Dendritic cell(s)
DSMC: Data Safety Monitoring Committee
ER: Extended-release
FCT: Film coated tablets
HANDs: HIV-associated neurocognitive disorders
HIV: Human immunodeficiency virus
hsCRP: Highly sensitive C-reactive protein
HVLT-R: Hopkins Verbal Learning Test Revised
IDO: Indoleamine 2,3-dioxygenase
IFN-α: Interferon-alpha
IFN-γ: Interferon-gamma
IL: Interleukin
IP-10: Interferon gamma-induced protein 10
IR: Immediate-release
Kyn: kynurenine
LPS: Lipopolysaccharides
mAb(s): monoclonal antibody/antibodies
MUHC: McGill University Health Centre
PBMCs: Peripheral blood mononuclear cells
PMA: Phorbol 12-myristate 13-acetate
POMS: Profile of Mood State
QoL: Quality of life
RNA: Ribonucleic acid
SMAQ: Simple Medication Adherence Questionnaire
Th17 cells: T helper 17 cells
Treg cells: T regulatory cells
Trp: Tryptophan
TrpOx: Tryptophan oxidation
ULN: Upper limit of normal
WBC: White blood cell
WHOQOL-HIV BREF: World Health Organization quality of life instrument in patients with HIV infection brief
XLC-MS/MS: Extraction-liquid chromatographic-tandem mass spectrometry.
